### Study assessments

The primary efficacy assessment is the change in HbA1c levels from baseline. Secondary efficacy assessments include changes in FPG, the percentage of patients with HbA1c ≤6.5%, the percentage with HbA1c ≤6.5% without GI side effects, and changes in 2-hour PPG levels. Exploratory assessments include body weight, the serum lipid profile, and β-cell function.

Safety assessments include any AEs, serious AEs, unexplained elevations of liver enzymes, hypoglycemic events, physical examination findings, vital signs, height and weight, laboratory determinations (hematological and biochemical parameters, urine analysis), electrocardiogram, pregnancy and reproductive ability evaluation, appropriateness of the safety tests, and other indexes such as a standard meal test.

Patients will be assessed at visit 1 (week −4), visit 2 (baseline), visit 3 (week 4), visit 4 (week 12), and visit 5 (week 24). Patients will be instructed to fast overnight and not take the study drug before the visits at these times. The schedule of assessments is provided in Table 3. At visit 1, demographic information, the patient’s relevant medical history and history of diabetes and its complications (including the date when diabetes was confirmed; the presence or absence of proliferative retinopathy, non-proliferative retinopathy, nephropathy, neuropathy, or foot ulcers; and the dates these complications were confirmed) will be collected. Thyroid-stimulating hormone levels will also be evaluated at this visit. As there is no central laboratory for the study, all parameters will be tested locally.

**Table 3 T3:** Schedule of assessments

**Visit**	**1**	**2**	**3**	**4**	**5**^**a**^
**Week**	**−4**	**Baseline**^**b**^	**4**	**12**	**24**
**Screening:**					
Informed consent	X				
Inclusion/exclusion criteria	X	X			
Height	X				
Thyroid-stimulating hormone	X				
**Demography/baseline data:**					
Demographic information	X				
History of diabetes and its complications	X				
History/current status	X	X			
**Treatment evaluation:**					
Drugs dispensed	X	X	X	X	
Drug count/check		X	X	X	X
Dosage records – metformin	X	X	X	X	X
Dosage records – vildagliptin		X	X	X	X
Currently receiving antihyperglycemic drugs	X				
Concomitant medicines	X	X	X	X	X
**Validity assessment:**					
HbA1c^c^	X	X		X	X
Fasting plasma glucose	X	X	X	X	X
Postprandial glucose^d^		X			X
Insulin^d^		X			X
Body weight	X	X	X	X	X
Standard meal test		X			X
**Safety evaluation:**					
Physical examinations	X	X			X
Vital signs	X	X	X	X	X
Electrocardiogram examination	X				X
Hematology examinations	X	X			X
Serum amylase		X	X	X	X
Standard biochemical tests^e,f^	X	X		X	X
Liver function tests^f^			X		
Pregnancy test^g^	X				X
Routine urine test		X			X
Adverse events	X	X	X	X	X
**Study end**					X

^a^Must also be taken in case of early withdrawal.

^b^Baseline =1st day of study.

^c^Determination of the HbA1c level with no central laboratory requires high-performance liquid chromatography.

^d^Only in the standard meal group.

^e^Standard biochemical examinations include, but are not limited to, the following: fasting blood glucose, liver function, kidney function (serum creatinine and blood urea nitrogen), and lipids (cholesterol and triglycerides).

^f^Liver function tests include ALT, AST, total and direct bilirubin, and alkaline phosphatase.

^g^Pregnancy tests specifically designed for women of childbearing potential.

HbA1c: glycated hemoglobin.

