## Materials and methods

### Subjects

Male and female Chinese T2DM patients (WHO/IDF criteria [38]) aged >18 years with HbA1c levels ranging between 6.5% and 9.0% and BMI between 22 and 45 kg/m^2^ at visit 1 who have received metformin at a stable dose of 750–1000 mg daily for at least 12 weeks before screening will be enrolled in the study. The patients will be required to maintain their individual eating and exercise habits during the study, and to follow all the study requirements. Written informed consent will be obtained from each patient prior to enrollment. Exclusion criteria for the study are listed in Table 1.

**Table 1 T1:** Exclusion criteria for the VISION study

	
**1.**	Pregnant or lactating women
**2.**	Medical history of following diseases:
	• Type 1 diabetes mellitus or diabetes caused by pancreatic injury or secondary diabetes: Cushing syndrome or acromegaly
	• Acute complications of diabetes: ketoacidosis or non-ketotic hyperosmolar coma within the past 3 months
	• Acute infections within 4 weeks prior to the screening (visit 1) that may affect the efficacy and safety of the study
	• Any obvious diabetic complications such as symptomatic autonomic neuropathy, gastroparesis, worsening hyperglycemia in the absence of any comorbid illnesses, and conditions that may affect blood glucose
	• History of kidney disease or clinical diagnosis of renal insufficiency indicated by serum creatinine ≥132 μmol/L (≥1.5 mg/dL) in males, and ≥123 μmol/L (≥1.4 mg/dL) in females
	• History of a liver disease such as cirrhosis, hepatitis B, or hepatitis C (except carriers) or Alanine transaminase (ALT), aspartate aminotransferase (AST) greater than 2 times the ULN or total bilirubin greater than 2 times the ULN
	• History of acute and chronic pancreatitis
	• Malignant tumor in the past 5 years, including leukemia and lymphoma (except for carcinoma in situ of the skin)
	• Torsades de pointes ventricular tachycardia or persistent, clinically relevant ventricular tachycardia or ventricular fibrillation or second-degree atrioventricular block (Mobitz type I and II) or third-degree atrioventricular block, or QTc prolongation (>500 ms)
	• Myocardial infarction, coronary artery bypass surgery or percutaneous coronary intervention, unstable angina, or stroke within the past 6 months
	• Congestive heart failure requiring medical treatment
**3.**	Fasting plasma glucose >15 mmol/L (>270 mg/dL) at visit 1

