**4.**	Clinically significant thyroid-stimulating hormone levels outside the normal range at visit 1
**5.**	Use of concomitant medications:
	• Other antihyperglycemic agents besides metformin within 12 weeks of visit 1
	• Long-term glucocorticoids (>7 consecutive days of treatment) within 4 weeks of visit 1
	• Treatment with growth hormone or similar drugs
	• Treatment with class Ia, Ib, or Ic, or class III antiarrhythmics
	• Treatment with any drug with known and frequent toxicity to a major organ system within the past 3 months
**6.**	Use of other investigational drugs at visit 1, or within 30 days or 5 half-lives of visit 1, whichever is longer
**7.**	History of active substance abuse (including alcohol) within the past 2 years
**8.**	Potentially unreliable patients or patients who, in the opinion of the investigator, are unsuitable for the study

ULN: upper limit of normal.

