**Figure 1 F1:**
[figure not shown]
Design of the VISION study.

Patients participating in the study will be subgrouped (1:1:1:1) based on their BMI and age into 4 groups: (1) <60 years and BMI <24 kg/m^2^; (2) <60 years of age and BMI ≥24 kg/m^2^; (3) ≥60 years of age and BMI <24 kg/m^2^; and (4) ≥60 years of age and BMI ≥24 kg/m^2^. In each group, patients will be randomized according to the study design. At visit 1, patients meeting the inclusion criteria will be assigned to open-label metformin 500 mg bid for a 4-week lead-in period. At visit 2, patients will be randomized in a ratio of 5:1 to receive either vildagliptin 50 mg bid plus metformin 500 mg bid (Group A) or metformin 500 mg tid (Group B) for the next 4 weeks. From visit 3 to the end of the study, Group A patients will continue to receive the maintenance dose of vildagliptin 50 mg bid plus metformin 500 mg bid, while group B patients will receive metformin 1000 mg bid.

The primary, secondary, and exploratory objectives of the study are shown in Table 2. The study drug will be discontinued if it shows unsatisfactory efficacy at week 12 (i.e., FPG >13.3 mmol/L [240 mg/dL]) confirmed by a repeated measurement in the absence of any concurrent illness. Worsening of glucose levels in the absence of any other explainable concurrent disease or emergency condition that can affect glucose levels, the occurrence of AEs including GI side effects or clinically significant changes in laboratory parameters, or an abnormality that, in the opinion of the investigators, requires immediate withdrawal of treatment, will also lead to the study drug being discontinued. An inexplicable increase in levels of liver enzymes (aspartate transaminase, alanine aminotransferase and total bilirubin) without any clinical signs that is confirmed by a repeat measurement within 3 working days, pregnancy, severe or frequent hypoglycemia (i.e., unexplained hypoglycemic events requiring the assistance of another person or >3 hypoglycemic events within a week), treatment with prohibited concomitant medications, or any other deviation from the treatment protocol will also lead to treatment discontinuation. The reason for a patient discontinuing treatment will be recorded in the case report form.

**Table 2 T2:** Primary, secondary, and exploratory objectives of the VISION study

	
**1.**	**Primary objective:**

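### No pregnancy test is scheduled at visit 2, so randomization and the first vildagliptin dose rely on a result four weeks old

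*Protocol article*

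**What the plan says.** The schedule of assessments (Table 3) places visits 1 to 5 at weeks -4, 0 (baseline), 4, 12 and 24. Under its safety evaluation heading, the row "Pregnancy test^g^ X X" is marked at visits 1 and 5 only. Footnote g limits the test to women of childbearing potential, and footnote a applies the visit 5 assessments to early withdrawal as well.

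The Table 3 row "Inclusion/exclusion criteria" is marked at visits 1 and 2, so eligibility is confirmed again after the lead-in. The first exclusion criterion in Table 1 is "Pregnant or lactating women", with no visit attached. Criteria 3 and 4 do carry one: "Fasting plasma glucose >15 mmol/L (>270 mg/dL) at visit 1" and "Clinically significant thyroid-stimulating hormone levels outside the normal range at visit 1".

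The Study design section gives all patients open-label metformin 500 mg bid for four weeks from visit 1. It continues: "At visit 2, patients will be randomized in a ratio of 5:1 to receive either vildagliptin 50 mg bid". That arm stays on its lead-in metformin dose, while the comparator arm steps up to three 500 mg doses a day. In line with this, the Table 3 row "Dosage records – vildagliptin" is first marked at visit 2. The same section lists pregnancy among the reasons for stopping treatment.

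**The concern.** Visit 2 is the last point at which an ineligible patient can be kept out of the randomized trial, and it is when exposure to the new drug begins. Pregnancy status can change during a four-week lead-in, and a test taken at the start of that period cannot reveal the change. A woman who conceives in those weeks and does not know it could pass the visit 2 eligibility check. She would then start vildagliptin (5 chances in 6) or a higher metformin dose (1 in 6), although the protocol means to exclude pregnant women.

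What is at stake is participant safety and the reliability of one eligibility criterion, not the statistical inference.

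**Working it through.** The plan states no figure of its own on this point, so the check is a reading of the schedule followed by simple arithmetic.

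**1. Is the row read correctly?** The marks in the pregnancy-test row fall under the first and fifth visit columns. Neighbouring rows read sensibly against the same five columns: physical examination at visits 1, 2 and 5, and electrocardiogram at visits 1 and 5. The blank at visit 2 is therefore part of the printed schedule.

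**2. Does another part of the article place a test at visit 2?** The Study assessments section names an evaluation of pregnancy and reproductive ability among the safety assessments but gives no visit for it. Table 3 repeats the history/current status item at visit 2, but that is a review, not a test. The routine urine test at visit 2 is a separate row from the pregnancy test. No scheduled pregnancy test at visit 2 was found.

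**3. Age of the result at randomization.** Age = week of visit 2 minus week of the latest scheduled test.
- As printed: 0 - (-4) = 4 weeks.
- With a visit 2 test: 0 - 0 = 0 weeks.

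**4. Who is concerned.** Inputs are the 828 patients per age/BMI stratum and four equal strata (Sample size estimations; Study design), and the 5:1 allocation.
- Total: 4 × 828 = 3312.
- Two strata under 60 years: 2 × 828 = 1656, which is 50% of 3312.
- Of these, on vildagliptin: 1656 × 5/6 = 1380. On metformin alone: 1656 - 1380 = 276.

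The two strata aged 60 or over are taken to contain practically no women of childbearing potential.

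**5. Number of added tests.** The article does not give the share of women of childbearing potential, so a range is assumed for the strata under 60 years. Tests = share × 1656, and the vildagliptin part is 5/6 of that.

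| Assumed share | Women tested at visit 2 | Of whom starting vildagliptin |
|---|---|---|
| 5% | 83 | 69 |
| 10% | 166 | 138 |
| 20% | 331 | 276 |
| 30% | 497 | 414 |

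These are counts of tests. They are not counts of pregnancies or of women wrongly randomized. The article gives no pregnancy rate, so neither of those can be computed.

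**The case against.** The strongest reply is that nothing in the article is violated. No maximum age for the pregnancy result is set, and rechecking a criterion need not mean repeating its test. A test is done at visit 1, before the first study metformin is given. At visit 2 eligibility and current status are both reviewed, a suspected pregnancy can be tested at any time, and pregnancy stops treatment. Contraception rules and the definition of childbearing potential are matters that an article commonly leaves to the full protocol, so the remaining risk cannot be judged from this document.

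Most of this stands, and it limits the point to an improvement. It does not remove the point. The article does fix the test visits, and it leaves blank the visit at which the new drug starts. A review of status depends on the woman already suspecting a pregnancy. The test before the first metformin dose does not cover vildagliptin or the metformin increase four weeks later.

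Three stronger readings are tempting, and the documents do not support them.
- A reader might infer that the protocol contradicts itself by rechecking criteria without retesting. It nowhere says that the recheck includes a test.
- A reader might infer that pregnancy alone is left untested among the exclusions without a visit limit, because kidney and liver function are measured again at visit 2 through the row "Standard biochemical tests^e,f". The QTc exclusion also has no visit limit, and the electrocardiogram is likewise scheduled at visits 1 and 5 only. The biochemistry panel is repeated at visits 4 and 5 too, so its visit 2 mark may be routine monitoring.
- A reader might infer that the long interval to visit 5 calls for further on-treatment tests. The stopping rule can act without a scheduled test, and that interval does not bear on eligibility at randomization.

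**Conclusion.** The point holds as a low-cost safety improvement. As printed, the latest scheduled pregnancy result is 4 weeks old when patients are randomized and start vildagliptin or a higher metformin dose, and it cannot show a conception during the lead-in. Pregnancy is an exclusion that is not confined to visit 1, and eligibility is rechecked at visit 2, so a current result at that visit would serve the protocol's own intention.

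The benefit is real but not quantified. The number of pregnancies that a visit 2 test would detect is unknown and probably small. The 83 to 497 women in the table rest on an assumed share of 5% to 30% and on equal strata of 828. A reader might take them as women harmed or put at risk, but they only show how many would be tested. A visit 2 test can also miss a conception in the last days of the lead-in, so it narrows the gap without fully closing it. Power, type I error and the primary analysis are untouched.

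**What to change.** In the pregnancy-test row of Table 3, add a mark at visit 2 for women of childbearing potential. Add to footnote g that the visit 2 result must be known before randomization.

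The cost is one inexpensive test per such woman, about 83 to 497 tests in all under the 5% to 30% assumption. Table 3 already schedules urine and blood tests at visit 2, and all testing is done locally, so no new visit is needed. The analysis does not change.

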### Data analysis

Intention-to-treat (ITT) analysis will be performed. The full analysis set (FAS) will include all randomized patients who took the study drugs at least once and had at least 1 primary or secondary efficacy evaluation after baseline. For assessment of missing primary efficacy variables, the last observation carried forward (LOCF) technique will be used. The per-protocol set (PPS) will include ITT patients completing at least 22 weeks of treatment, and those who discontinued the study due to a poor therapeutic response (FPG >13.3 mmol/L [240 mg/dL]) after 12 weeks of treatment, provided they have no major protocol deviations and had a valid assessment of HbA1c levels within 7 days after their last dose of study drug. Any major deviation from the protocol will be identified and documented in the analysis plan. Patients will be analyzed in the treatment group to which they were randomly assigned for the efficacy assessment.

The safety analysis set (SAS) will include patients who took the study drugs at least once and had at least 1 safety assessment after baseline. The safety analyses will be according to the patients’ treatment, and will include the description of any AEs.

The FAS set will be used as the primary population for the primary efficacy variable, the change from baseline in HbA1c levels at 24 weeks. The primary efficacy variable will be analyzed using an analysis of covariance (ANCOVA) model and the LOCF approach.

Non-inferiority of the study drug will be analyzed using the null hypothesis and a unilateral alternative hypothesis, which are defined as follows:

$$H_{0},\delta_{\mathrm{vildagliptin}}\geq \delta_{\mathrm{metformin}}+0.3\%$$

$$H_{a},\delta_{\mathrm{vildagliptin}}<\delta_{\mathrm{metformin}}+0.3\%$$

where δ represents the change from baseline.

In order to control the overall type I error at alpha = 0.05, a sequential test procedure along with the Hochberg procedure will be employed. Non-inferiority testing for the overall population will be performed first. After achieving non-inferiority for the overall population, non-inferiority testing for the 4 subgroups will then be performed. Secondary efficacy variables include percentages of patients achieving therapeutic goals at the study endpoint: HbA1c ≤6.5%, HbA1c ≤6.5% without GI side effects, and absolute decreases in HbA1c from baseline of ≥1%, ≥0.7%, and ≥0.5%. In the FAS and PPS populations, the percentages of patients achieving the therapeutic goals will be analyzed and compared between treatment groups using the Chi-square test.

To assess the robustness of the results of the primary efficacy analysis, i.e., the change from baseline in HbA1c at 24 weeks, an ANCOVA model with LOCF will be used for the PPS. For the primary and secondary efficacy endpoints, subgroup analyses based on age and BMI will be performed.

Safety analyses will include summaries of AEs, changes from baseline in vital signs, the number of subjects with post-baseline laboratory values that will fall outside predetermined ranges, and the frequency and severity of hypoglycemic events. Adverse events will be summarized by system organ class and preferred terms. Summaries of AEs by severity and by relationship to study drug will also be provided.

The incidence of patients with any GI events will be compared between treatment groups using Fisher’s exact test.

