As recommended in the traditional stepwise approach, intensification of therapy with higher doses has shown to be successful in improving glycemic control. However, the increased risk of AEs with dosage increases has resulted in impaired patient compliance and subsequently poor glycemic control [12]. For example, metformin therapy is associated with dose-dependent GI adverse effects such as diarrhea, flatulence, and abdominal discomfort, which often lead to treatment discontinuation [18,19]. In the UKPDS 33 study, intensive treatment with sulfonylureas or insulin was associated with an increased incidence of hypoglycemia and weight gain [20]. Moreover, the stepwise approach can also cause a delay in switching from monotherapy to combination therapy, which often leads to further deterioration of glycemic control [1,15,19].

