	• To demonstrate that the change from baseline in HbA1c levels after 24 weeks of treatment with vildagliptin 50 mg bid as add-on therapy to metformin 500 mg bid is non-inferior to high-dose metformin
**2.**	**Secondary objectives:**
	• To demonstrate in predefined patient subgroups [based on body mass index (BMI <24 and ≥24 kg/m^2^) and age (<60 and ≥60 years)] that vildagliptin add-on therapy to metformin is non-inferior to high-dose metformin in the change from baseline in HbA1c levels
	• To determine the percentages of patients achieving the target HbA1c level of ≤6.5% in the two treatment arms of the overall population and in the predefined subgroups
	• To determine the percentages of patients achieving the target HbA1c level of ≤6.5% in the two treatment arms of the overall population and in the predefined subgroups
	• To determine the mean change from baseline to 24 weeks in fasting plasma glucose in the overall population and in the predefined subgroups
	• To determine the mean change from baseline to 24 weeks in 2-hour postprandial glucose in a subsample of 464 patients with type 2 diabetes mellitus
	• Safety analysis
**3.**	**Exploratory objectives:**
	• To determine the mean change from baseline to 24 weeks in body weight and lipid parameters in the overall population and in the predefined subgroups
	• To determine the change from baseline to 24 weeks in β-cell function in a subsample of 464 patients with type 2 diabetes mellitus

BMI: body mass index; HbA1c: glycated hemoglobin.

Treatment will also be discontinued if the patient cannot tolerate the GI symptoms associated with a dose increase at visit 2. If patients in Group B cannot tolerate the GI symptoms at visit 3, the dose of metformin can be decreased by one tablet (250 mg) until the GI symptoms improve. After that, the dose will be gradually increased over 1–2 weeks. The dose of the metformin in Group B will be at least 500 mg bid until week 12. After week 12 (visit 4), dose adjustments of metformin will not be allowed at any time. Adjustment of the vildagliptin dose will not be allowed throughout the study.

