Patients discontinuing the study drug, including those who do not attend the last visit, will be assessed for safety within 30 days of receiving their last dose. If all randomized patients complete the 24-week, open treatment period, the study will be considered completed. Premature termination of the study will be notified to the institutional review boards and/or ethics committees.

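### Fixing LOCF as the primary missing-data method is likely to favour non-inferiority if the metformin arm loses as many or more patients early

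*Protocol article*

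**What the plan says.** **Primary analysis.** Under Data analysis, the 24-week HbA1c change is analysed by ANCOVA on the FAS, with this rule for missing data: "For assessment of missing primary efficacy variables, the last observation carried forward (LOCF) technique will be used". The same section promises an intention-to-treat analysis. It admits to the FAS any treated patient who "had at least 1 primary or secondary efficacy evaluation after baseline". FPG is a secondary efficacy assessment, so a week-4 FPG alone is enough.

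**Robustness.** The one stated check is the same ANCOVA with LOCF on the PPS. That set needs 22 or more weeks of treatment, or stopping for poor response after week 12.

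**Stopping rules (Study design).** At visit 2 Group B goes from metformin 500 mg bid to 500 mg tid, while Group A stays at 500 mg bid and adds vildagliptin. The text then says: "Treatment will also be discontinued if the patient cannot tolerate the GI symptoms associated with a dose increase at visit 2". A general rule, covering both arms, lists "the occurrence of AEs including GI side effects or clinically significant changes in laboratory parameters" as grounds for stopping.

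**HbA1c timing.** The last two visits are "visit 4 (week 12), and visit 5 (week 24"). Table 3 marks HbA1c at visits 1, 2, 4 and 5 and not at week 4. Footnote a, attached to visit 5, reads "Must also be taken in case of early withdrawal". For patients who stop study drug, the Study design text says only that they "will be assessed for safety within 30 days of receiving their last dose".

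**Expected losses.** The Background states that "metformin therapy is associated with dose-dependent GI adverse effects such as diarrhea, flatulence, and abdominal discomfort, which often lead to treatment discontinuation".

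**The concern.** LOCF treats the last HbA1c before loss as the week-24 result. If that value was taken a few weeks after randomization, most of the treatment effect has not yet appeared in it. A Group B patient who stops under the visit 2 rule before visit 3 has not even reached the 1000 mg bid comparator dose, yet enters the comparison as a week-24 result for that arm.

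In a superiority trial, shrinking an arm's effect is often tolerated as cautious. Here it works the other way: an understated control reduction makes it easier to show that vildagliptin add-on is no worse by 0.3. The article's own Background gives a reason to expect early GI losses where the metformin dose rises.

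The stake is the primary claim and, through the sequential procedure, access to the four age/BMI subgroup tests.

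**Working it through.** **Inputs from the article.** Margin 0.3 (hypotheses in Data analysis); SD 1, one-sided 0.05 and 90% power (Sample size estimations); allocation 5:1; 3312 randomized; overall dropout 20%, not split by arm.

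**The plan's own figure.** Control patients per subgroup = (1 + 1/5) × (1.645 + 1.282)² × SD² / margin². With margin 0.3 this is 1.2 × 8.56 / 0.09 = 114.2, so 115 control and 6 × 115 = 690 in total, which matches the printed 690. With the 0.5 printed in the sample size section it gives 42 control and 252 in total, which does not match. The two margins are a separate matter. The calculation below uses 0.3, which stands in the hypotheses and reproduces 690.

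**Standard error, overall population.** 3312 split 5:1 is 2760 and 552. SE = sqrt(1/552 + 1/2760) = 0.0466.

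**Bias at the null boundary.** Let E_B be the control reduction at week 24 on treatment and E_A = E_B − 0.3 the vildagliptin reduction. Let d_B and d_A be the shares lost early, and f the fraction of the week-24 effect already present in the carried value.

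Bias toward non-inferiority = (1 − f) × (d_B × E_B − d_A × E_A)

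Actual one-sided error = Φ(−1.645 + bias / SE)

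**Illustration.** Assumed, not in the article: E_B = 0.6 (so E_A = 0.3), d_B = 15%, d_A = 5%. Then d_B × E_B − d_A × E_A = 0.09 − 0.015 = 0.075.

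| Fraction f captured | Bias | Bias / SE | One-sided error (nominal 0.05) |
|---|---|---|---|
| 0 | 0.075 | 1.61 | about 0.49 |
| 0.5 | 0.0375 | 0.80 | about 0.20 |
| 0.8 | 0.015 | 0.32 | about 0.09 |

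**Range over other assumptions** (f from 0 to 0.8):
- Loss 15% (B) and 5% (A), E_B from 0.5 to 1.0: bias 0.013 to 0.115, error 0.086 to 0.794.
- Equal loss of 5%: bias = (1 − f) × 0.05 × 0.3 = 0.003 to 0.015, error 0.057 to 0.093.
- Equal loss of 20% (the planned overall dropout, if all of it were early): bias 0.012 to 0.060, error 0.083 to 0.360.
- Opposite direction: E_B = 0.7, f = 0, loss 5% (B) and 20% (A) gives 0.035 − 0.080 = −0.045, error 0.005.

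So at the boundary equal loss already inflates the error, and the sign reverses only if Group A loses clearly more patients.

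**At the planning assumption of no true difference.** The margin is 0.3 / 0.0466 = 6.4 standard errors away. With equal effects of 0.6, the same losses and f = 0, the bias is (0.15 − 0.05) × 0.6 = 0.06. That moves the distance to 0.36 / 0.0466 = 7.7 standard errors. Non-inferiority would be concluded either way.

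**The case against.** The other side has several good points.

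- **Not only the control arm.** A reader might infer that GI stopping is built into Group B alone. That is true, in practice, of the visit 2 dose-increase rule only; the general adverse-event rule reaches both arms. Group B may also reduce its dose for GI symptoms at visit 3, which limits stopping after that step.
- **Not necessarily baseline carried forward.** A reader might infer that early stoppers score zero change. Footnote a requires the visit 5 assessments, HbA1c included, at early withdrawal, so the carried value should usually be an early on-treatment one. Nor does the article say that a baseline value may be carried; a patient with only an FPG might simply drop out of the ANCOVA. The f = 0 row is therefore a near worst case for those loss rates.
- **The target matters.** If the aim is the outcome regardless of stopping, and stoppers drift back to baseline, a carried near-baseline value could be nearly right. This fits the intention-to-treat wording. But the primary objective is framed as the effect of 24 weeks on treatment, and the article describes no week-24 HbA1c after stopping that would support the other target.
- **The PPS is some check.** It removes the early carried values at issue. It does so by selecting patients who stayed, so it is a partial check and not an analysis under a different missing-data assumption.
- **Left to the SAP.** Further sensitivity analyses may be there, and their absence from the article is no fault. The choice of LOCF as primary, however, is fixed in the article.

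These points reduce the likely size. They do not remove the direction when Group B loses at least as many patients early.

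**Conclusion.** The concern stands as a likely anti-conservative bias, not a demonstrated one. It needs early loss in Group B at least as high as in Group A, which the article's account of dose-dependent GI effects makes plausible, and an on-treatment target.

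On the assumptions shown, the bias is 0.015 to 0.075, or 5% to 25% of the 0.3 margin, and the one-sided error at the boundary rises from 0.05 to between about 0.09 and 0.49. Loss by arm, the control effect and the fraction captured at withdrawal are all assumed.

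A reader might conclude that the bias decides the trial. The documents do not support that: it matters when the true difference lies near the margin and has little effect near 0, where the trial was planned. A claim that LOCF also makes the standard errors too small has not been quantified here and is not part of the conclusion.

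**What to change.** 1. Make the primary analysis a likelihood-based repeated-measures model on all HbA1c values (baseline, week 12, withdrawal, week 24), or multiple imputation, adjusted for baseline HbA1c and age/BMI group. State how withdrawal values are placed in time.
2. Keep ANCOVA with LOCF as a sensitivity analysis.
3. Do not let a patient whose only post-baseline efficacy value is an FPG enter the primary HbA1c analysis with baseline carried forward. Include such patients through the model or the imputation.
4. State whether the target is the effect on treatment or the outcome regardless of stopping. If the latter, also collect week-24 HbA1c in patients who stop study drug and use it in the analysis.

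Cost: items 1 to 3 are changes of wording and modest analysis work. Item 4, if chosen, is a protocol change with one extra follow-up visit for patients who stop, because their visit 5 assessments are otherwise done at withdrawal. The estimate may be less favourable to vildagliptin. No dose or stopping rule is affected.
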